## Study Summary

**Study purpose:** to assess the effectiveness of Amitriptyline compared to placebo in the management of moderate to severe HIV- related peripheral neuropathy in a population using ARV and not using ARV therapy

**Study design:** A double blind randomised controlled trial using a cross over design

**Sample Size:** 124 participants; 62 on ARV therapy and 62 not on ARV therapy followed up for a total of 15 weeks

**Study population:** adult men and women with documented HIV infection and moderate to severe HIV related distal sensory neuropathy

Visit schedule: An information session with recruitment, followed by a screening visit and an enrolment visit. After enrolment there will be five scheduled visits and weekly telephonic follow-up if written consent provided for that. Optional visits to the Palliative care centres may be done at any time during office hours for concerns, advice or further information. After hours telephonic contact will be available.

Study duration: the total duration of the study is 14 months. Three months for start up, training and preparation, enrolment closes after 6 months; the last participant exiting at month 11, and three months analysis and write up.

Primary objective: A measurement of the difference in pain intensity at the beginning and end of each 6 week treatment period.

Secondary objective: These will be adverse side effects of treatment, minimum effective doses, maximal tolerated doses, mood and effect on activities of daily living.

Study sites: Participants will be recruited from the Nthabiseng HIV Clinic at the Chris Hani Baragwanath Hospital, the Helen Joseph Hospital HIV clinic, and the palliative care clinic and outreach services.

Regulatory and monitoring: The Medicines Control Council (MCC) approval is not required since the drug is being used for indicated purposes. The MCC will be notified. The trial will be registered with the SA National Trials Register, and the Cochrane trials register. Ethical approval will be sought from the Wits REC and regular progress reports submitted as well as SAE, AEs and protocol violations. A study DSMB will be constituted who will perform an interim analysis as well as monitor the trial for safety and protocol violations.

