### ***Follow up procedures: Day 4-day 15***

At home: one tablet will be taken at night for three nights. On the third day the study nurse will call to enquire as to adverse effects, pain score and any other problems, and advice on the next dosage. If the pain has abated significantly the dose will be left at one tablet at

night. If not, the dose will be increased to two tablets at night for three nights. The same procedure will occur until a maximum of 6 tablets at night has been reached. The participant will continue to take this dose for 4 weeks. A weekly telephone call will be conducted by the study nurse.

|                         |                                                                                                                                                                                                                                                                                                   |
|-------------------------|---------------------------------------------------------------------------------------------------------------------------------------------------------------------------------------------------------------------------------------------------------------------------------------------------|
| Day 3                   | The study nurse will call to enquire as to adverse effects, pain score and any other problems, and advice on the next dosage. If the pain has abated significantly the dose will be left at one tablet at night. If not, the dose will be increased by two tablets at night for three nights.     |
| Day 7                   | The study nurse will call to enquire as to adverse effects, pain score and any other problems, and advice on the next dosage. If the pain has abated significantly the dose will be left at two tablets at night. If not, the dose will be increased to three tablets at night for three nights.  |
| Day 11                  | The study nurse will call to enquire as to adverse effects, pain score and any other problems, and advice on the next dosage. If the pain has abated significantly the dose will be left at three tablets at night. If not, the dose will be increased to four tablets at night for three nights. |

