| Day 13                  | The study nurse will call to enquire as to adverse effects, pain score and any other problems, and advice on the next dosage. If pain has abated significantly the dose will be left at four tablets at night. If not the dose will be increased to six tablets at night. I                       |
| Week 3 day 15           | The study nurse will call to enquire as to adverse effects, pain score and any other problems, and advise to stay at the same dosage for the next 4 weeks                                                                                                                                         |
| Visit 3.0 Week 3 day 21 | Visit to study site. Check diary, questionnaire administered, medication check, discussion and information as required with participant, reimbursement, referral as required                                                                                                                      |
| Week 4 day 28           | The study nurse will call to enquire as to adverse effects, pain score and any other problems, and advise to stay at the same dosage for the next 3 weeks                                                                                                                                         |

|                         |                                                                                                                                                                                                                                                                                                                                                                                                                                                                                                             |
|-------------------------|-------------------------------------------------------------------------------------------------------------------------------------------------------------------------------------------------------------------------------------------------------------------------------------------------------------------------------------------------------------------------------------------------------------------------------------------------------------------------------------------------------------|

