| Visit 9.0 Week 9 day 63 | Visit to study site Check diary, questionnaire administered, medication check, discussion and information as required with participant, reimbursement, referral as required. Patient to receive new drug pack                                                                                                                                                                                                                                                                                               |
| Week 10 Day 66          | The study nurse will call to enquire as to adverse effects, pain score and any other problems, and advice on the next dosage. If the pain has abated significantly the dose will be left at one tablet at night. If not, the dose will be increased to two tablets at night for three nights.                                                                                                                                                                                                               |
| Day 69                  | The study nurse will call to enquire as to adverse effects, pain score and any other problems, and advice on the next dosage. If the pain has abated significantly the dose will be left at two tablet at night. If not, the dose will be increased to three tablets at night for three nights.                                                                                                                                                                                                             |

|                                                                   |                                                                                                                                                                                                                                                                                                                                                                                                                                                            |

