|-------------------------------------------------------------------|------------------------------------------------------------------------------------------------------------------------------------------------------------------------------------------------------------------------------------------------------------------------------------------------------------------------------------------------------------------------------------------------------------------------------------------------------------|
| Week 11 day 72                                                    | The study nurse will call to enquire as to adverse effects, pain score and any other problems, and advice on the next dosage. If the pain has abated significantly the dose will be left at three tablets at night. If not, the dose will be increased to four tablets at night for three nights.                                                                                                                                                          |
| Day 75                                                            | The study nurse will call to enquire as to adverse effects, pain score and any other problems, If not, the dose will be increased to six tablets at night.                                                                                                                                                                                                                                                                                                 |
| Day 78                                                            | The study nurse will call to enquire as to adverse effects, pain score and any other problems, and advice to stay on the same dosage for the next 4 weeks.                                                                                                                                                                                                                                                                                                 |

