### **Guidelines for introducing amitriptyline**

Patients in this group will be given amitriptyline according to the following protocol. The dose of the drug will not be affected by the weight of the patient.

| Dose                                                                 | Days   |
|----------------------------------------------------------------------|--------|
| 25mg od at night
increase the dose on next visit if pain persists | Day 0  |
| 50mg od at night
increase the dose on next visit if pain persist  | Day 3  |
| 75mg od at night
increase the dose on next visit if pain persist  | Day 7  |
| 100mg od at night                                                    | day 11 |
| 150 mg od at night                                                   | Day 15 |

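### The titration instructions contradict each other on step size, on step days and on the contact at which the dose is changed

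*Protocol*

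**What the plan says.** The dose ladder in Amitriptyline for HIV related DSN runs 25, 50, 75, 100 and 150 mg. Follow up procedures: Day 4-day 15 expresses it in tablets, up to a maximum of six.

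- **Step at Day 3, period 1.** The running text says "If not, the dose will be increased to two tablets at night for three nights". The Day 3 row of the table below it says "If not, the dose will be increased by two tablets at night for three nights". The Day 66 row, which is the same step in period 2, agrees with the running text.
- **Step at Day 7, period 1.** The row presumes a patient on two tablets: "If the pain has abated significantly the dose will be left at two tablets at night".
- **Step at Day 11, period 1.** "If not, the dose will be increased to four tablets at night for three nights". The next call is on Day 13.
- **Top step.** In period 1 the Day 13 row says "If not the dose will be increased to six tablets at night", and the Day 15 row tells the patient to hold the dose. In period 2 the top step is in the Day 75 row: "If not, the dose will be increased to six tablets at night". The table in Guidelines for introducing amitriptyline puts 150 mg at Day 15.
- **Contact.** The visit table changes the dose at nurse telephone calls. The Guidelines table says "increase the dose on next visit if pain persists". The Study Summary provides for "weekly telephonic follow-up if written consent provided for that".

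**The concern.** These are working instructions that a nurse reads out and a patient acts on. Where two of them give a different number of tablets on the same day, staff must choose, and different staff may choose differently.

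There are two consequences. The first is for participant safety: the passages disagree on how large the first step is and on when the maximum is reached. The second is for the outcomes. Secondary outcome measures include the minimum efficacious dose and the maximal tolerated dose, and both are read from the step a patient has reached. A patient moved from one tablet to three never passes through the two-tablet level, so a response or an intolerance at two tablets cannot be recorded there.

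The difference in step days between the periods also raises the question whether exposure differs enough between them to matter for the crossover comparison.

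**Working it through.** **Inputs.** Step days and tablet counts come from the visit table in Follow up procedures. Milligram steps come from the Guidelines table. Period 2 begins at the Day 63 visit, so period day = study day − 63. Tablet strength is not stated. It is inferred as 150 mg / 6 tablets = 25 mg, which agrees with one tablet and 25 mg as the starting doses.

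**The stated top-dose day.** The Guidelines table gives Day 15. Neither visit table reproduces it: period 1 gives Day 13 and period 2 gives 75 − 63 = period day 12. On Day 15 the Guidelines table steps up, while the visit table holds the dose.

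**Period day on which each step begins:**

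| Source | 2 tablets | 3 tablets | 4 tablets | 6 tablets |
|---|---|---|---|---|
| Period 1 table, Day 3 read as *to* two | 3 | 7 | 11 | 13 |
| Period 1 table, Day 3 read as *by* two | skipped | 3 | 11 | 13 |
| Period 2 table (Days 66, 69, 72, 75) | 3 | 6 | 9 | 12 |
| Guidelines table, converted at 25 mg | 3 | 7 | 11 | 15 |

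**Size of the Day 3 conflict.** *By* two gives 1 + 2 = 3 tablets (75 mg). *To* two gives 2 tablets (50 mg). The literal reading also clashes with the Day 7 row. A patient on three tablets whose pain has abated would be left at two, which is a reduction. One whose pain has not abated would be increased to three, which is no change.

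**Step length.** The Day 3, 7 and 11 rows each describe a step of three nights. The following calls are 7 − 3 = 4, 11 − 7 = 4 and 13 − 11 = 2 days later. In period 2 the spacing is three days throughout.

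**Day 75 row.** Every earlier step first states what happens if pain has abated. This row omits that branch, so its opening words have no condition to refer back to, at the step to the maximum.

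**Contact.** The Guidelines table attaches a next-visit rule to its Day 0, 3 and 7 rows. The first scheduled follow-up visit is Day 21, so no visit exists at which those steps could be made.

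**Exposure for a patient who steps up every time.** Cumulative dose = 25 mg × the sum of (nights × tablets), over 42 nights:

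- Period 1, *to* two: 3×1 + 4×2 + 4×3 + 2×4 + 29×6 = 205 tablets = 5,125 mg.
- Period 1, *by* two: 3×1 + 4×3 + 4×3 + 2×4 + 29×6 = 209 tablets = 5,225 mg.
- Period 2: 3×1 + 3×2 + 3×3 + 3×4 + 30×6 = 210 tablets = 5,250 mg.
- Guidelines table: 3×1 + 4×2 + 4×3 + 4×4 + 27×6 = 201 tablets = 5,025 mg.

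Period 2 exceeds period 1 (*to* two) by 125 mg, which is 125 / 5,125 = 2.4%. Over the first 15 nights the totals are 1,200 and 1,075 mg, a difference of 125 / 1,075 = 12%. The percentages do not depend on the assumed tablet strength. Nights at six tablets are 29, 29, 30 and 27 in the order listed.

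**The case against.** The best defence is that the intended scheme can be recovered. One word in the Day 3 row stands against the running text, the Day 7 row, the Day 66 row, the ladder and the Guidelines table, so it looks like a slip. The lost branch in the Day 75 row can be supplied from the rows before it. The next-visit rule sits close to other text that does not fit this trial: Side effects describes a six-week study and Limitation of the study an open one. It may be left over from another design. Protocol violations also promises written operating procedures, which are not shown and may settle the matter. All of this is fair and explains how the conflicts may have arisen. It does not remove them, and it does not settle the top-dose day, on which three sources differ.

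Two stronger readings are tempting.

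- **The two periods deliver different treatments.** The documents do not support this. Both periods use the same 1-2-3-4-6 ladder, the same maximum and once-nightly dosing, and the visit tables differ by one night at the top step. The visit window of 3 days either side is wider than that. Both randomised sequences follow the same schedule within a period, so the mismatch acts mainly as a period difference.
- **A patient who declines telephone contact stays at one tablet until Day 21, which dilutes the effect.** This is conjecture. The Study Summary makes *weekly* calls conditional on consent. The titration calls are more frequent, and the running text lists the weekly call separately. Participants also have a number to call and may attend in office hours, and Side effects describes weekly nurse monitoring at which the dose may be increased. No passage says that titration calls may be declined.

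**Conclusion.** The point holds as an internal contradiction in the dosing instructions. The sources conflict on the Day 3 step (by one tablet), on the top-step day (period day 12, 13 or 15), on step days between periods (3, 7, 11, 13 against 3, 6, 9, 12), on step length, and on whether steps are made by telephone or at a visit. The Day 75 row also lacks its condition. No reader can comply with all of these at once.

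The stake is clarity of dosing, with a bearing on safety and on the minimum-efficacious and maximal-tolerated dose outcomes. The stake for the primary comparison is small: about 2.4% of cumulative dose between the two visit tables, at least 27 nights at the top step in every version, and no bias in the drug-placebo contrast from this source alone. The milligram figures assume 25 mg tablets, and the totals assume a patient who steps up at every opportunity. Which step size or day is right is a clinical decision and is not judged here.

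**What to change.** Reconcile the ladder in Amitriptyline for HIV related DSN, the running text and both halves of the visit table in Follow up procedures, and the Guidelines for introducing amitriptyline into one titration table used identically in both periods. The clinical team decides the steps and days. In that table, give the number of tablets after each step as a total and state the tablet strength. Make the interval between contacts match the stated length of each step, and give both branches at every step, including the last.

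Name the contact at which each step is made. State whether the consent condition on weekly telephone follow-up in the Study Summary also covers the titration calls and, if it does, how the dose is titrated for a patient who declines. No new eligibility criterion is needed.

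The cost is one table and a sentence or two, with matching edits to any operating procedure copied from the present text. Sample size, visit schedule and analysis are unaffected.

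### The period-1 Day 3 titration row raises the dose by two tablets where two in total is meant; the Day 75 row lacks its hold condition, and the day of the 150 mg step differs between tables

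*Protocol*

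**What the plan says.** The dosing rule appears in several places in the Protocol.

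- **Follow up procedures, narrative.** Participants start on one tablet at night. If pain has not abated significantly at the first call: "If not, the dose will be increased to two tablets at night for three nights. The same procedure will occur" until six tablets are reached.
- **Same section, Day 3 row (period 1).** "If not, the dose will be increased by two tablets at night for three nights".
- **Same section, Day 7 row.** If pain has abated, "the dose will be left at two tablets at night. If not, the dose will be increased to three tablets at night".
- **Same section, Day 13 row.** If pain has abated, "the dose will be left at four tablets at night. If not the dose will be increased to six tablets at night".
- **Same section, Day 66 row (period 2, counterpart of Day 3).** "If not, the dose will be increased to two tablets at night for three nights".
- **Same section, Day 75 row (period 2, counterpart of Day 13).** The row lists the enquiries and then gives the rise to six tablets as the alternative to a condition that is not stated.
- **Amitriptyline for HIV related DSN.** The ladder has five steps: 25, 50, 75, 100 and 150 mg.
- **Guidelines for introducing amitriptyline.** The Day 3 dose is "50mg od at night"; 100 mg is on Day 11 and 150 mg on Day 15.

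**The concern.** The table rows tell the study nurse what to advise at each call. The Day 3 row is grammatical and explicit, so a nurse working from that row alone would give a dose that the rest of the protocol does not intend. The first rise would then be 75 mg in period 1 and 50 mg in period 2 of the same crossover. A participant taken from 25 to 75 mg would also never try 50 mg, so that step could not be identified as that participant's minimum efficacious or maximal tolerated dose. Both are listed under Secondary outcome measures.

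The Day 75 omission concerns the step to the maximum dose. As printed, the row gives no circumstance in which a participant whose pain is controlled on four tablets stays there.

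**Working it through.** **Tablet strength.** It is not stated outright. Setting the tablet counts in the call table against the ladder gives 25/1 = 50/2 = 75/3 = 100/4 = 150/6 = 25 mg per tablet at every step.

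**Day 3 dose, five statements side by side.**

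| Place | Instruction | Dose |
|---|---|---|
| Narrative | to two tablets | 2 × 25 = 50 mg |
| Day 66 row | to two tablets | 2 × 25 = 50 mg |
| Ladder, second step | 50 mg | 50 mg |
| Introduction table, Day 3 | 50 mg | 50 mg |
| Day 3 row | by two tablets | (1 + 2) × 25 = 75 mg |

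The Day 3 row stands alone. It triples the starting dose (75/25 = 3) where a doubling is intended (50/25 = 2). The excess is 75 − 50 = 25 mg, a ratio of 75/50 = 1.5.

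**Check against the next row.** The Day 7 row offers two outcomes: stay at two tablets or rise to three. For someone already on three, the first would be a reduction and the second no change. The row can be followed only from two tablets, so two was meant.

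**How long the excess lasts.** Day 3 to Day 7 is 7 − 3 = 4 days. A participant still in pain at Day 7 is then due three tablets (75 mg) on the intended schedule, and the excess ends. It could last longer only in someone whose pain abates between the two calls and who is kept on three tablets.

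**Day 75.** The Day 13 row has a hold at four tablets and then the rise to six. The Day 66, 69 and 72 rows each have a hold too. Day 75 has only the rise, from 4 × 25 = 100 mg to 6 × 25 = 150 mg.

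**Day of the 150 mg step.** The call table gives six tablets at the Day 13 call; the introduction table gives 150 mg on Day 15, a gap of two days. A related mismatch is that the Day 11 row says "the dose will be increased to four tablets at night for three nights", yet 13 − 11 = 2 nights pass before the Day 13 call.

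**The case against.** The strongest reply is that the document corrects itself. The narrative directly above the Day 3 row and the Day 7 row directly below it both show two tablets, and on Day 75 the words that follow make no sense without the missing clause. Under Protocol violations, standard operating procedures are to be written from the protocol and signed off by staff, which gives a chance to catch both slips. This is fair, and it limits the weight of the point. It does not remove it, because a procedure copied from the table would carry the wrong dose forward. Whether the Day 75 clause was lost in drafting or in reading the PDF cannot be settled from the extracted text, so the source table should be checked.

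A reader might infer more in three ways.

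- **That participants held at a lower dose will later jump over ladder steps**, because each titration row after Day 3 names fixed tablet counts. The documents do not support this. The narrative repeats the same procedure at each call, and the Trial abstract describes titration to effect or to a maximum dose. The introduction table raises the dose if pain persists, and Side effects allows the dose to be maintained or increased. The Day 15 and Day 78 rows fit any dose. A skipped step is not clearly prescribed anywhere.
- **That the Day 3 row is a serious safety problem.** The section headed Placebo treats 25 to 75 mg as a low dose, so the concern is only that 75 mg is reached at the first rise without trying 50 mg.
- **That the primary comparison is biased.** The rows make no distinction between active drug and placebo packs, and the usual excess ends by Day 7, 42 − 7 = 35 days before the Day 42 visit. The documents give no basis for claiming bias.

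**Conclusion.** The Day 3 row is wrong as written and conflicts with four other statements of the same dose. The Day 75 row is incomplete, and the 150 mg step has two different days. These are wording errors in dosing instructions and are worth correcting before the table is used.

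The size is small: 25 mg above the intended dose from Day 3, usually for four days. It would reach only participants whose pain had not abated by Day 3 of period 1, and only if the row were followed literally. The protocol gives no rate of early relief, so no number affected can be estimated; the enrolment target of 124 is only a ceiling. The conclusion assumes 25 mg per tablet, which matches all five ladder steps. The sample size and the primary drug-placebo contrast are not in question.

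**What to change.** 1. In the Day 3 row, change the rise so that it is to two tablets, as in the Day 66 row.
2. In the Day 75 row, restore the hold at four tablets, using the Day 13 wording.
3. Use one day for the 150 mg step in the call table and in Guidelines for introducing amitriptyline. Day 13 keeps the existing calls, but the Day 11 row should then say two nights. Day 15 allows the three nights but moves the step to a later call.
4. Optionally, add one sentence saying that any later rise after a hold is one ladder step from the current dose. This is a clarification only, and the Day 15 and Day 78 rows can stay as they are.

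The cost is an edit to two tables and to any operating procedure already copied from them. No extra participants or visits are needed, and with Day 13 no call moves.

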### **Side effects**

Side effects will be continually monitored throughout the study as part of symptom control. (Appendix IV)

| Amitriptyline |
|----------------------|
| Dry mouth            |
| Sedation             |
| Weight gain          |
| Confusion            |
| Dizziness            |
| Palpitations         |
| Constipation         |

|       |
|-------|
| Other |
|-------|

Patients who develop side effects will be assessed by a doctor. Patients assessed as having serious adverse events will be withdrawn from the study, and reasons recorded. The total period of the study will be 6 weeks from enrolment. After being enrolled, subjects will be monitored for pain relief, symptom control and quality of life by the nurse, after which an intervention will be put in place. Monitoring will be done weekly by a professional nurse. Intervention can be one of the following:

- Increase the dose, and continue with the trial
- Maintain the dose, and continue with the trial
- Stop the drug because of adverse events, and drop from the study

For those that have been found to be not effective, alternative treatment will be offered.

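### Phoned dose increases depend on pain alone and are not tied to the side-effect assessment, so a patient with persisting pain and a side effect falls under conflicting instructions

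*Protocol*

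**What the plan says.** Under Follow up procedures, the nurse telephones during the first two weeks or so of each treatment period, asks about adverse effects, pain and other problems, and advises on the next dose. The Day 7 row then gives the rule: "pain has abated significantly the dose will be left at two tablets at night. If not, the dose will be increased to three tablets". Days 3, 11, 66, 69 and 72 have the same form. Day 13 takes the dose to its maximum on the same basis: "If pain has abated significantly the dose will be left at four tablets at night. If not the dose will be increased to six tablets".

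Two rows are damaged. Day 75, the counterpart of Day 13, has no pain clause left: "pain score and any other problems, If not, the dose will be increased to six tablets at night". Day 3 says "the dose will be increased by two tablets at night for three nights", whereas the paragraph above the table and the Day 66 row both raise the dose *to* two tablets.

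The table under Guidelines for introducing amitriptyline attaches to its 25, 50 and 75 mg rows the instruction to "increase the dose on next visit if pain persists" (with trivial variation). Its 100 and 150 mg rows carry no condition.

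The Side effects section says that side effects are monitored throughout, that a doctor assesses patients who develop them, and that those with serious adverse events are withdrawn. Patients are monitored for "symptom control and quality of life by the nurse, after which an intervention will be put in place"; the options are to increase, to maintain, or to stop for adverse events. It adds: "Monitoring will be done weekly by a professional nurse". It does not mention the titration calls, and they do not mention it.

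**The concern.** Whether to raise or hold the dose of a sedating drug is decided by a nurse on the telephone, and the only criterion in the call rows is pain. The Side effects list includes confusion, dizziness and palpitations. If a patient whose pain is unchanged reports one of these, the call row points to a higher dose while the Side effects section points to a doctor. Nothing says which comes first.

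What is at stake is patient safety during titration. The top dose is 150 mg. The section on clinical issues in choosing the drug cites good tolerability only up to 100 mg a day. The Placebo section expects few side effects at 25 to 75 mg. The 150 mg in the amitriptyline section is the upper end of a range in which other trials showed effect, which is not evidence of tolerability.

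**Working it through.** **Dose ladder.** One tablet is 25 mg, so 1, 2, 3, 4 and 6 tablets give 25, 50, 75, 100 and 150 mg. This reproduces the ladder in the amitriptyline section and in the dose table.

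**Condition for each increase.**

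| Step (mg) | Call, period 1 | Call, period 2 | Condition in the call rows | Condition in the dose table |
|---|---|---|---|---|
| 25 to 50 | Day 3 | Day 66 | pain, both | pain |
| 50 to 75 | Day 7 | Day 69 | pain, both | pain |
| 75 to 100 | Day 11 | Day 72 | pain, both | pain |
| 100 to 150 | Day 13 | Day 75 | pain at Day 13; none left at Day 75 | none |

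That is 4 + 4 = 8 rows that can raise the dose: 7 with a pain condition, 1 without, and 0 with a side-effect condition.

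**Timing against site visits.** The last increase is at Day 13 in period 1. In period 2 it is at Day 75, which is 75 − 63 = 12 days after the Day 63 visit at which the new pack is issued. The next scheduled site visits are Day 21 and Day 82, so 21 − 13 = 8 and 82 − 75 = 7 days later. With the 3-day visit window the earliest attendances are 21 − 3 = 18 and 82 − 3 = 79, still after the top dose. The dose table puts 150 mg at Day 15, also before Day 18. The whole rise, 150 / 25 = 6-fold, can therefore be made by telephone.

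**Pace.** Contacts in period 1 fall on Days 0, 3, 7, 11, 13 and 15, with gaps of 3, 4, 4, 2 and 2 days. In period 2 they fall on Days 63, 66, 69, 72, 75 and 78, with gaps of 3 days throughout. After any increase the next scheduled call is 2 to 4 days away. The step from 100 to 150 mg is the largest in mg (50 against 25 for the others). It is not the largest in relative terms: 25 to 50 mg is +100%, and 50 to 75 mg is +50%, the same as 100 to 150 mg. It follows 13 − 11 = 2 days at 100 mg in the call table, or 15 − 11 = 4 days in the dose table.

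**The Day 3 slip.** Adding two tablets to one gives 3 tablets, 75 mg. The intended dose is 2 tablets, 50 mg, because the Day 7 row assumes that the patient is on two.

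**The two sections side by side.**

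- Pain abated, with or without a side effect: the call row holds the dose. No conflict over escalation.
- Pain persists, no side effect: both allow an increase.
- Pain persists, serious adverse event: the Side effects section withdraws the patient, so the outcome is stated even though the call row does not mention it.
- Pain persists, non-serious side effect: the call row says increase. The Side effects section says a doctor assesses, and the dose may be increased, maintained or stopped, with no criterion for maintaining it in this case and no timing relative to the call. The instructions are unreconciled.

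The fault lies in the fourth case.

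**The case against.** The strongest reply is that the call rows are only part of the rule. The Side effects section is equally operative: it provides continual monitoring, a doctor's assessment and an option to maintain or stop. With the exception of Day 75, where the dose-advice phrase has dropped out, every titration row puts the adverse-effect question before the advice on dose. Maximal tolerated dose is a secondary outcome, so dosing limited by tolerability is evidently intended. Optional visits, after-hours telephone contact and extra visits for adverse events are also available.

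Much of this stands. A reader might infer that a patient reporting confusion must be given the next increase in that same call, or that tolerability has no place in the dosing. The documents support neither: the nurse asks, and could hold under the Side effects section. Nor does the weekly monitoring there mean that side effects go unasked between weekly points, since each titration call asks about them.

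The reply does not supply a written hold. The sentences after the enquiry fix the dose on pain, and no answer about side effects changes them. Access to extra visits does not alter the rule either. The side-effect form (Appendix IV) and the standard operating procedures are not shown and may contain a hold. However, the Protocol violations section says that the procedures are written from the approved protocol, so the protocol should state it.

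**Conclusion.** The point holds as a conflict between two sections on a safety decision, confined to patients with persisting pain and a non-serious side effect. None of the eight increase rows has a side-effect condition, and neither does the dose table. Read literally, the call rule permits escalation to 150 mg before the next scheduled site visit in either period.

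This rests on the protocol text alone and assumes that no unseen appendix or procedure already supplies the hold. How many patients would be escalated despite a side effect cannot be derived, because no side-effect rates during titration are given. A reader might go on to infer harm to the primary pain comparison or to the maximal tolerated dose outcome; nothing here establishes either. The Day 3 and Day 75 wordings are drafting slips, worth correcting in the same edit because staff would act on them. The sponsor should make the change.

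**What to change.** In all eight titration rows (Days 3, 7, 11, 13, 66, 69, 72 and 75) and in the dose table, state: *increase only if pain persists and no side effect needing medical assessment is reported; otherwise hold the dose until the doctor's assessment described under Side effects.*

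Say which side effects trigger the hold. The Side effects section as written sends any side effect to a doctor, and mild dry mouth alone need not stop titration. Restore the pain clause at Day 75 and correct Day 3 to read *to* two tablets. Apply the rule identically in both periods so that blinding is kept.

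A cross-reference in the maintenance calls, where the Day 15 row tells the nurse to "advise to stay at the same dosage for the next 4 weeks", is optional: those calls do not raise the dose, and the option to stop already applies.

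The cost is small: no new visit or form and no change in sample size. Some dose steps will be delayed, which shortens time at the final dose for those patients. Doctor contacts will come earlier, but the protocol already requires them.
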